#### Description of sample characteristics - comorbidities

Comorbidities are assessed by the “**Self Administered Comorbidity Questionnaire**” (SACQ) [29,30]. Participants are asked to comment on 12 frequent medical conditions (heart disease, high blood pressure, lung disease, diabetes, ulcer or stomach disease, kidney disease, liver disease, anemia or other blood disease, cancer, depression, arthritis, and back pain). For each medical condition patients are asked whether they suffer from this problem, if he/she receives treatment for it, and if the problem causes functional limitations. The test-retest reliability for the SCQ was 0.94 (95% confidence interval: 0.72 to 0.99) as calculated by the intra class correlation coefficient [29]. Regarding validity, the Spearman correlation between the SACQ and the Charlson Index was 0.55 for the instrument [29].

#### Description of sample characteristics - psychosomatic symptoms

To identify psychosomatic symptoms, we use the somatization subscale of the “**Symptom Check-List-90-R”** (SCL-90-R) [31]. It is a commonly used psychological status symptom inventory for mental illness. It is built up of nine dimensions: somatization, obsessive compulsive, interpersonal sensitivity, depression, anxiety, anger/hostility, phobic anxiety, paranoid ideation and psychoticism. The instrument supports the computation of three overall scales, comprising the number of symptoms in general and their mean impact. Items are rated on the 5-point Likert Scale of distress, ranging from “not at all” to “extremely”. Schmitz et al. described a high reliability (internal consistency of somatization subscale α = 0.81) and a moderate concurrent validity compared to the “General Health Questionnaire” (0.52) [32].

#### Risk factor - anxiety and depression

The “**Hospital Anxiety and Depression Scale**” (HADS) [33,34] screens for anxiety disorders and depression. It consists of two 7-item subscales (anxiety and depression). Each item scores on a four-point Likert scale and assesses symptoms in the last week. Psychometric properties of the HADS were assessed in numerous studies. Herrmann et al. reported high reliability of the anxiety and depression subscales (internal consistency anxiety α = 0.80; depression α = 0.81) as well as high validity (correlated with external anxiety scales r = 0.65; depression scales r = 0.70) of the German version of HADS [34].

#### Protective factor - coping resources for back pain

We use the FBR-questionnaire “**Fragebogen zu Bewältigungsressourcen bei Rückenschmerzen”** from Tamcam et al. to assess coping resources for back pain [35]. It was specially developed for identifying helpful coping resources of patients with back pain in primary care setting. While other scales rather ask for the knowledge of pain coping skills and resources, the 12-item-FBR explicitly asks for their perceived helpfulness [35]. Items are rated on an eleven-point Likert scale ranging from “not helpful” to “very helpful”.

#### Protective factor - resilience

**Resilience** as a potential protective factor towards pain generalisation is estimated using the resilience scale RS-11, a shortened and validated German form of the Wagnild & Young questionnaire [36,37]. It measures the capacity to withstand life stressors. We use the 11-item short version of the 25-item original scale. It consists of two subscales (Personal Competence and Acceptance of Self and Life). Reliability testing by Schumacher et al. proved high internal consistence (α = 0.91). In addition, validity of RS-11 was demonstrated by a high correlation with the construct of self-efficacy [37].

### Supplementary baseline measurements for CWP patients

CLBP patients, having CWP at baseline, get supplementary concluding measurement instruments (SES, Brief COPE, GSE, PDS-d-1, critical life events, apart from therapy course, medication, MPI and body pain drawing model), like the cohort group gets during follow ups. Taking into account the length of the questionnaires they are assessed after 3 months. An extensive description of the measurement instruments and our motivation for using it is described in the next chapter.

### Follow up measurements for CLBP patients (cohort group)

To identify incidental CWP (primary outcome), we collected data every three months to screen for pain generalization using the **body pain drawing** model (T0-T4).

In addition the following physical and psychological parameters are collected at follow up (Table 2):

#### Description of sample characteristics - pain perception

We assess pain perception with the “**Schmerzempfindungsskala**” (SES) during the first follow up [38]. The questionnaire consists of 24 items with two global dimensions “affective aspects of pain perception” and “sensory aspects of pain perception”. The items ask for different pain perceptions (for example: “My pain feels hot.”) and patients have to judge their degree of agreement on a four-point Likert scale ranging from “not true” to “absolutely true”. Psychometric tests showed high reliability (internal consistency of the affective subscale/sensory subscale α = 0.92/α = 0.81) and good validity [38].

#### Description of sample characteristics - health care utilization and medication

Just like at baseline, **health care utilization and medication** during the preceding half year are assessed after the 6th and 12th month (T2 and T4).

During the 12 months follow up the following data will be collected:

#### Protective factor - coping

To assess stress management competence (coping), we use the **Brief COPE** from Carver et al. [39,40]). It is a shorter version of the original COPE questionnaire and consists of 14 subscales, where each subscale is represented by two items. Participants are asked to think of their usual thoughts and actions while faced with a difficult situation and to indicate their answers on a four-point Likert-type scale, rating the resemblance of each item to coping efforts pursued. The response scale ranges from “not at all”, “a little bit”, “considerably” to “very much”. Cooper et al. tested reliability of Brief COPE to patients with Alzheimer’s disease. They assessed average internal consistencies for emotion-focused (α = 0.72), problem-focused (α = 0.84), and dysfunctional (α = 0.75) subscales [41]. Regression analyses indicate convergent and concurrent validity [41].

#### Protective factor - self-efficacy

We use the “**general self-efficacy-questionnaire”** (GSE) to assess self-efficacy [42,43]. It applies to a patient’s self-assessment of their ability to improve their daily troubles and how they cope with critical situations. The questionnaire consists of 10 items to be rated by four-point-Likert-scale ranging from “very uncertain”, “rather uncertain”, “rather certain” to “very certain”. Hintze et al. showed a high reliability (internal consistency α = 0.92) and good validity (correlation with the resilience scale r = 0.68) of the German version of GSE [43].

#### Risk factor – trauma

We use Part 1 of the “Posttraumatic Diagnostic Scale” (PTDS) [44] to assess whether patients suffer from traumatic life events. It is a self-report screening instrument based on the type, time duration, and circumstances of traumatic experiences [45]. Griesel et al. reported high reliability (internal consistency of the total scale was α = 0.94) and high validity (correlation with the “Clinician Administered PTSD Scale” (CAPS) r = 0.76; p = 0.001) of the German PTDS [45].

#### Risk factor - critical life events

The **critical life events** questionnaire from the work of Leist et al. are used [46]. Participants are asked to select if and when they experienced any possibly life changing events on a 22 items list.

#### Description of sample characteristics - pain characteristics

Finally, during the fourth follow up measurement point (T4) participants are asked to complete the “**West Haven-Yale Multidimensional Pain Inventory**” [25,26]. This is done to investigate if our CLBP patients can be classified into the three clusters (dysfunctional, interpersonally distressed, adaptive copers) that have been widely shown to represent different subgroups of patients with fibromyalgia [47].

### General practitioners case report

GPs are asked to comment on the individual presence of red flags with every patient included in the study. Red flags are frequently used risk factors for identifying serious disorders causing low back pain [48]. In addition, we ask GPs for their personal opinion about whether the patient’s prognosis will be better, equal or worse in one year. GPs are asked to estimate each patient’s probability for pain generalization during the follow up.

### Qualitative sub-study

Based on the results of the cohort study a qualitative sub-study will be performed, after completed follow up, regarding patients’ and physicians’ perspectives of a resource based treatment approach for prevention and therapy of CLBP and CWP.

### Statistical analysis

Group comparisons of CWP and CLBP patients will be performed. For this we use measures of central tendency (mean and standard deviation, median, percentile, frequency and percentages) as well as chi-square tests for categorical data. The *t*-test is applied for comparing means. Effect sizes will be expressed in terms of odds ratios for categorical dependent variables and, for quantitative dependent variables, in terms of group differences or differences per unit change of a quantitative predictor variable.

For identification of predictors logistic regression analysis will be performed using incidental CWP as dependent variable. We use baseline risk and protective factors as independent variables or predictors. All analyses are supervised and advised by a senior statistician of the Institute of Genetic Epidemiology (IGE), University of Munich and Helmholtz Zentrum München.

Focus groups: The results of the focus groups are analyzed according to predefined main topics. Answers of patients and physicians are contrasted.

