**Methods/Design:**

Fifty-nine general practitioners recruit consecutively, during a 5 month period, all patients who are consulting their family doctor because of chronic low back pain (where the pain is lasted for 3 months). Patients are asked to fill out a questionnaire on pain anamnesis, pain-perception, co-morbidities, therapy course, medication, socio demographic data and psychosomatic symptoms. We assess resilience, coping resources, stress management and self-efficacy as potential protective factors for pain generalization. Furthermore, we raise risk factors for pain generalization like anxiety, depression, trauma and critical life events. During a twelve months follow up period a cohort of CLBP patients without CWP will be screened on a regular basis (3 monthly) for pain generalization (outcome: incident CWP).

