### Aim of the study

The aim of our study is to provide prevalence data on CLBP and CWP for the primary care setting. The differences between both pain localizations, with respect to pain characterisation and comorbidities, will be determined. In addition, we search for risk factors and protective factors of pain generalization in primary care CLBP patients.

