### Study population

For a multi centre data collection, general practitioners in the State of Hessen, Germany are approached. Due to logistical reasons, recruitment is conducted in four waves. Participating practices (doctors and assistant personnel) are asked to recruit all eligible patients who consult for CLBP during a 5 months period, including patients consulting in home visits and emergency calls. Detailed inclusion and exclusion criteria are shown in Table 1. Trained clinical monitors visit the practices to insure validity and consecutive recruitment, during two times (at beginning and at half time of recruitment period).

**Table 1 T1:** Inclusion- and exclusion criteria

**Inclusion criteria**	All patients with chronic* low back pain** as a primary or secondary consulting reason in general practice.
	*”chronic” was defined as pain during most days in the last three months.
	**”low back pain” means pain in the back area under the costal arch, but over the bottom fold (with or without pain radiation).
**Exclusion criteria**	- patients under 18 years
	- pregnant women
	- persons with insufficient fluency of speaking German language or dementia (subjective impressed by doctor)

The number of patients, who deny participation is documented along with the reasons (in an anonymized way), and these patients are accounted for our prevalence analyzes.

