### Sample size

Based on results from previous studies we presumed a CWP prevalence of 10% [49] leading to 900 patients to be included in the cohort study (localized chronic pain only). Assuming a 10% rate of patients developing generalized pain (n = 90) [50] up to 9 independent variables may be included in the logistic regression analysis (corresponding to 10 events per independent variable [51,52]).

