## Discussion

This cohort study will be the largest study which prospectively analyzes predictors for transition from CLBP to CWP in primary care setting. In contrast to the typically researched risk factors, which increase the probability of pain generalization, this study also focus intensively on protective factors, which decrease the probability of pain generalization. The identified risk and protective factors might aloud GPs to identify patients at risk for development of CWP. Furthermore, the acquired knowledge about protective factors will help us to develop an individualized treatment approach for GPs.

Selection bias is often the major limitation of a cohort study. The amount of psychological constructs measured in this study can be rather demanding in terms of endurance and intellectual abilities compared to usual studies in primary care setting. For our primary care study population, which includes a high proportion of older people and persons with lower educational background, it may be a problem to deal with the questionnaires. These patients might be more likely to deny participation or abort follow up.

It might be possible, that GPs are more likely to remember study recruitment, in special cases (e.g. patients with higher disease severity or special characters) or during times with a lower workload. An incomplete recruitment brings forth the risk of selection bias and lowers external validity.

Results of the baseline analysis are expected in the course of this year (2012). Follow up data will be completed, next year (2013).

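### Patients are nested in 59 GPs, but only independence-based methods are named; prevalence and incidence intervals computed that way would be too narrow, while predictor tests would change little

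*Protocol article*

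**What the plan says.** The abstract (Methods/Design) describes the recruitment: "Fifty-nine general practitioners recruit consecutively, during a 5 month period". The Study population section confirms the multi-centre structure: "For a multi centre data collection, general practitioners in the State of Hessen, Germany are approached".

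The Aim of the study section puts prevalence first: "The aim of our study is to provide prevalence data on CLBP and CWP for the primary care setting". The Sample size section presumes 10% CWP at baseline, "leading to 900 patients to be included in the cohort study", and expects 10% of these to develop CWP (90 events).

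For the analysis, the Statistical analysis section gives descriptive summaries "as well as chi-square tests for categorical data" and a t-test that "is applied for comparing means". For the cohort question it says: "For identification of predictors logistic regression analysis will be performed using incidental CWP as dependent variable". The Power calculation section adds a per-test alpha of 0.005 and a power of 0.83. None of these sections mentions GP, practice, a design effect, a random effect, GEE or robust standard errors.

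The Discussion allows that "GPs are more likely to remember study recruitment, in special cases (e.g. patients with higher disease severity or special characters", and that recruitment may depend on workload. It treats this as a matter of selection bias and external validity.

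**The concern.** Patients of one GP share a catchment area, a referral pattern and a recruiter, so their CWP status may be correlated. A chi-square test, a t-test and an ordinary logistic regression take each patient as a separate piece of information.

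A proportion estimated from clustered patients bears the full design effect, so an interval that ignores GP overstates the precision of the prevalence and incidence figures. The question for the predictor model is whether the same problem distorts the tests at 0.005.

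**Working it through.** **Inputs.** From the article: 59 GPs; 900 cohort patients; 10% CWP at baseline; 10% incident CWP; alpha 0.005. The baseline number follows as 900 / (1 − 0.10) = 1000. The article gives no ICC, so 0.01 to 0.05 is assumed here, with 0.10 as an extreme. Equal cluster sizes, one cluster per GP and complete follow-up are also assumed.

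**The plan's own figures.** 900 × 0.10 = 90 events, and 90 / 10 = 9 variables, as stated. 0.005 × 9 to 10 tests = 0.045 to 0.050, as stated. None of these figures contains an allowance for clustering. Whether the stated power follows from its inputs is a separate matter and is not used here.

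**Cluster size.** Baseline: 1000 / 59 = 16.95. Cohort: 900 / 59 = 15.25.

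**Prevalence and incidence.** DEFF = 1 + (m − 1) × ICC, and half-width = 1.96 × √(0.10 × 0.90 / n × DEFF).

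| ICC (assumed) | DEFF, baseline | Half-width, prevalence (n = 1000) | DEFF, cohort | Half-width, incidence (n = 900) |
|---|---|---|---|---|
| 0 | 1.00 | 1.86 points | 1.00 | 1.96 points |
| 0.01 | 1.16 | 2.00 | 1.14 | 2.10 |
| 0.02 | 1.32 | 2.14 | 1.29 | 2.22 |
| 0.05 | 1.80 | 2.49 | 1.71 | 2.57 |
| 0.10 | 2.59 | 3.00 | 2.43 | 3.05 |

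**Patient-level predictors.** Here the inflation depends on the product of two correlations: DEFF ≈ 1 + (m − 1) × ICC of outcome × ICC of predictor. In the cohort:

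- Low end (0.01 and 0.02): 1 + 14.25 × 0.0002 = 1.003.
- High end (both 0.10): 1 + 14.25 × 0.01 = 1.14.
- Standard errors therefore grow by about 0.1% to 7% (√1.14 = 1.07).
- By the same approximation the true size of a nominal 0.005 test is 0.0051 to 0.0086, the upper figure only at the extreme.
- If the stated power of 0.83 is taken as given, it falls to about 0.80 or stays above for most pairs of ICCs, and to 0.76 at the extreme.

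The baseline CWP versus chronic low back pain (CLBP) comparisons use the larger cluster size, which gives 1 + 15.95 × 0.01 = 1.16 at the same extreme.

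**Simulation check.** Logistic data were simulated with 59 clusters, n = 900, a GP effect on the logit scale, outcome ICC 0 to 0.10, predictor ICC 0.05 or 0.10, and 3000 runs per setting. Ordinary logistic regression rejected a true null in 0.004 to 0.006 of runs at nominal 0.005. The Monte Carlo standard error is √(0.005 × 0.995 / 3000) = 0.0013, so this cannot be told apart from nominal. A plain sandwich estimator with a normal reference rejected in 0.0067 to 0.0093 of runs, which bears on how the fix should be worded.

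**The case against.** The strongest reply is that this is a condensed article. It names families of tests and never says that patients will be treated as independent. Logistic regression is compatible with robust standard errors or a random intercept. A senior statistician supervises the analyses, and a variance estimator is often left to a fuller document. This stands in part: the article is silent on clustering and does not rule out an allowance. But it does commit to specific tests, a per-test alpha and a simulated power for patients recruited through 59 GPs, and a better-matched method is cheap to name.

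Several stronger readings are tempting, and the document does not support them:

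- **All standard errors are wrong.** The named tests concern variables that are expected to vary mainly within GPs, and the working shows that little changes for them.
- **The planned prevalence intervals are wrong.** No such interval, and no method for one, is stated. They would be too narrow only if computed under independence.
- **Tests for education, comorbidity and medication exceed 0.005.** Table 2 lists these as sample characteristics. The model takes baseline risk and protective factors, and Table 2 lists psychological and life-event constructs under those headings.
- **A practice term would remove confounding from selective recruitment.** Robust standard errors leave the estimates unchanged, and GEE or a random intercept does not generally remove between-practice confounding. The Discussion describes selection of patients that any GP might make, not a stated difference between practices. The design asks for consecutive recruitment of all eligible patients, with monitor visits.

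**Conclusion.** The point holds in limited form. The sampling is clustered, and the named methods make no allowance for it. For prevalence and incidence, an independence-based interval would be too narrow at any positive ICC. With an assumed ICC of 0.01 to 0.05, the half-width at 10% should be 2.0 to 2.5 points instead of 1.9 for prevalence, and 2.1 to 2.6 instead of 2.0 for incidence. If several GPs share a practice, the clusters are fewer and larger and the effect grows.

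For the group comparisons and patient-level predictors the expected effect is small: a design effect of about 1.00 to 1.14 over the assumed ICCs (up to 1.16 for the baseline comparisons), with no detectable loss of type I error control in simulation. The predictor conclusions are not threatened. All sizes rest on assumed ICCs.

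**What to change.** State in the Statistical analysis section that a GP or practice identifier is carried into the analysis data. Then:

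- Report CWP prevalence and 12-month incidence with cluster-robust 95% intervals.
- For the CWP versus CLBP comparisons and the incident-CWP logistic model, use standard errors clustered on GP or practice, or GEE. Name the level if GPs share practices.
- Add a small-sample correction, such as a t reference with clusters minus one (58) degrees of freedom or a bias-corrected sandwich. The uncorrected version was somewhat liberal at 0.005 in the simulation.

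GP fixed effects are impractical with 90 / 59 = 1.5 expected events per GP, and a random-intercept variance would be poorly estimated for the same reason.

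The cost is a change of wording, one identifier that recruitment already generates, and slightly wider intervals. No new patient data or change of design is needed.

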### Sample size

Based on results from previous studies we presumed a CWP prevalence of 10% [49] leading to 900 patients to be included in the cohort study (localized chronic pain only). Assuming a 10% rate of patients developing generalized pain (n = 90) [50] up to 9 independent variables may be included in the logistic regression analysis (corresponding to 10 events per independent variable [51,52]).

### Power calculation

Assumptions: Prevalence of generalized chronic back pain of 10%. A change of an independent variable by one standard deviation in the population implies an odds ratio of 1.65. Calculated power: 0.83 for alpha = 0.005, which means after adjustment of multiple testing of 9–10 variables an overall probability of the type one error of 0.05 will not be exceeded. The power has been calculated by performing simulations using the software R (R Development Core Team 2010).

### Ethics committee

The study was approved by the local ethics commission of Philipps-University Marburg (Ethik: 11.06.2010, AZ 88/10) and is in accordance with the Declaration of Helsinki.

